# Dietary Intake Nutritional Status and Lifestyle of Adolescent Vegetarian and Nonvegetarian Girls in New Zealand (The SuNDiAL Project): Protocol for a Clustered, Cross-Sectional Survey

**DOI:** 10.2196/17310

**Published:** 2020-05-27

**Keywords:** vegetarianism, teenagers, women, iron, zinc, calcium, B12, physical activity, attitudes motivations, beliefs

## Abstract

**Background:**

Anecdotally, vegetarian eating patterns seem to be increasing in parallel with growing concerns about environmental sustainability. While this pattern of eating is widely believed to be associated with benefits for the planet and individual health, it may increase the risk of inadequate intakes and nutrient deficiency if not planned carefully. Adolescent girls may be particularly at risk, as they have increased requirements for nutrients such as iron, zinc, calcium, and vitamin B12 during growth and development.

**Objective:**

The objective of the SuNDiAL Project (Survey of Nutrition, Dietary Assessment, and Lifestyles) is to compare the dietary intakes and habits, nutrition status, motivations, attitudes, and physical activity of a sample of vegetarian and nonvegetarian adolescent girls in New Zealand.

**Methods:**

A clustered, cross-sectional, nationwide study of adolescents aged 15-18 years was conducted. Secondary schools were recruited throughout New Zealand, and pupils (n=290) were invited to participate in data collection in either the first (February to April) or third (August to October) school term of 2019 (New Zealand schools operate on a 4-term year). Sociodemographic and health information; vegetarian status; dietary habits; and attitudes, motivations, and beliefs regarding food choices were assessed via an online self-administered questionnaire. Dietary intakes were collected via two 24-hour diet recalls on nonconsecutive days and will be adjusted for within-person variation using the Multiple Source Method, to represent usual intakes. Nutrient adequacy will be assessed by the estimated average requirement cut-point method or probability approach as appropriate. Height and weight were measured, and blood and urine samples collected for micronutrient status assessment. Participants wore an accelerometer for 7 days to assess 24-hour activity patterns (time spent asleep, sedentary, or engagement in light-intensity or moderate-to-vigorous intensity physical activity).

**Results:**

Recruitment and data collection were conducted in 2019. Data are currently being cleaned and analyzed, with publication of the main results anticipated at the end of 2020.

**Conclusions:**

The SuNDiAL Project will provide a meaningful and timely description of diet, nutrition status, and motivational factors associated with vegetarianism and identify any risks this pattern of eating may pose for female adolescents. The results of this study will support the development of targeted recommendations and interventions aimed at enhancing the health, growth, and development of adolescent girls.

**Trial Registration:**

Australian New Zealand Clinical Trials Registry ACTRN12619000290190; https://tinyurl.com/yaumh278

**International Registered Report Identifier (IRRID):**

DERR1-10.2196/17310

## Introduction

### Background

Few, if any, robust estimates of the prevalence of vegetarianism in populations exist, although plant-based and vegetarian diets (defined as not consuming any red meat, poultry, or seafood for the purposes of this article) appear to be growing in popularity. Increasing concern regarding the importance of environmental sustainability may explain this apparent rise; however, health is reported as a significant motivator for many vegetarians [1]. Indeed, vegetarians tend to have a body mass index that is 1-2 kg/m^2^ lower than their otherwise comparable nonvegetarian peers and exhibit less weight gain during adulthood [2]. Vegetarians also have a slightly lower risk of some cancers [2] and as much as a 24% lower risk of ischemic heart disease [2], presumably because they tend to have lower total and low-density lipoprotein cholesterol concentrations [2]. However, much of the data that underpin our understanding of how vegetarianism may affect disease incidence was collected from adult populations prior to the 1990s [3,4] or in the early 2000s [5]. Much less is understood about the foods and nutrient intake of vegetarian adolescents. Recent advances in food technology, food fortification, and the widespread availability of products designed to be plant-based substitutes for meat and milk imply that vegetarians can now choose from many commercially produced food products [6]. However, consistent with older research, more recent studies indicate that vegetarian or vegan eating patterns score higher on the healthy eating index due to a lower sodium and saturated fat intake and higher intakes of fruits and vegetables [7].

A well-planned vegetarian diet containing vegetables, fruits, whole grains, legumes, nuts, and seeds can provide adequate nutrition for most members of the population [8]. In general, vegetarian diets provide large amounts of phytate, dietary fiber, folate, vitamins C and E, and magnesium, but without planning, they may have low protein, vitamins D and B12, iron, zinc, and calcium (particularly among vegans who do not consume animal products of any kind) [8,9]. Additionally, while the iron and zinc content of a vegetarian diet may be similar to that of a nonvegetarian diet, the high phytate content, absence of heme iron from cellular animal sources, and lower animal protein intake reduces the bioavailability of iron and zinc, significantly increasing the risk of deficiency [10]. The risk of vitamin B12, calcium, iron, and zinc deficiency may be greater in certain sex and life-stage groups such as young female adults [10-12]. The pubertal growth spurt, sexual maturation, and the onset of menarche increase requirements for vitamin B12, calcium, iron, and zinc in adolescent girls [12]. Increased autonomy over food intake and reductions in energy intake due to a desire to lose weight or achieve a certain body type may further contribute to the risk of nutrient deficiencies in this age group that could be exacerbated in vegetarians without careful food choice. Indeed, the latest representative data collected in New Zealand over a decade ago indicates that 88% of female adolescents have inadequate intakes of calcium, and 34% have inadequate intakes of iron, with 11% being identified as having iron deficiency and a further 5% as having anemia [13], despite the estimation that less than 9% of this age group was likely to be vegetarian at the time of data collection [14].

Reasons for following a vegetarian diet include health [1], ethical and environmental concerns [1,15,16], animal welfare [1,15,16], and religious beliefs [16]. However, adolescent girls in New Zealand, who are already at risk of low calcium intakes and iron status, may be further increasing that risk if they do not follow a carefully planned vegetarian diet. It is crucially important to develop guidelines that mitigate the risk and maximize potential benefits, such as reducing saturated fat and increasing fiber intakes. Understanding the motivations, attitudes, and beliefs that underpin food choices is important to inform the development of appropriate and effective guidelines, in particular, to understand why some people choose to be vegetarian and others do not. Other lifestyle behaviors, such as physical activity, that may go hand-in-hand with food choices, should also be examined in relation to health risks and benefits of a vegetarian diet. This knowledge can then be used to appropriately and effectively communicate lifestyle recommendations for those following a vegetarian diet.

### Objectives

Anecdotally, vegetarianism appears to be increasing in popularity. While this increase in popularity may confer some health benefits to the population, adolescent girls in New Zealand are already at an increased risk of inadequate intakes of iron and calcium, which would clearly be exaggerated if animal products were avoided. A poorly planned vegetarian diet can increase the risk of some nutrient deficiencies that may be exacerbated in female adolescents. Therefore, it is critical that the nutrient intake and status of vegetarian adolescent girls are assessed. Furthermore, assessing motivations, attitudes, and beliefs will further our understanding of dietary choices and inform the development of health promotion materials and programs targeted to this age group.

The aim of the SuNDiAL Project (Survey of Nutrition, Dietary Assessment and Lifestyles) is to compare the dietary intakes and habits, nutrition status, motivations, attitudes, and physical activity of a sample of vegetarian and nonvegetarian adolescent girls in New Zealand. The objectives of this study are to describe and compare the following between vegetarians and nonvegetarians:

Dietary intakes of macronutrients, free and added sugars, phytate, fiber, and key micronutrients (iron, zinc, vitamin B12, folate, iodine, and calcium)Biochemical status of key micronutrients (iron, zinc, vitamin B12, and folate)Attitudes toward and motivations for food choice (eg, the environment, animal welfare, health)Twenty-four–hour activity patterns (sleep, sedentary behavior, and physical activity)Dietary habitsWeight loss intentions

## Methods

### Study Design

The SuNDiAL project is a nationwide cross-sectional survey of female adolescents aged 15-18 years. Nationwide data collection was achieved by utilization of a cohort of postgraduate research students. At the University of Otago, second-year Master of Dietetics students are required to undertake a 6-month research project in addition to 6 months of clinical placement. These student researchers are trained in dietary assessment and clinical skills, making them ideal data collectors for this study. In groups of 2-4 students, they collected data in locations convenient to their clinical placement or home city in New Zealand. In total, data were collected in 8 locations throughout New Zealand. The goal was to recruit at least one secondary school in each of Dunedin, Christchurch, Wanaka, Nelson, Wellington, Tauranga, Whangarei, and New Plymouth. These locations cover a range of cities from small (Wanaka) to large (Christchurch), from the south (Dunedin) to the north (Whangarei) of New Zealand. Data were collected in the first (February to April) or third (August to October) term of school in 2019 (New Zealand secondary schools operate on a 4-term year). The underlying ethnic makeup of the female population aged 15-18 years living in these areas is 70% New Zealand European, 17% Māori, 8% Pacific, and 15% Asian. Socioeconomic status information for this age group is not readily available in New Zealand. However, because we used a convenience sample, the final study population may differ from the overall population. This study has been approved by the University of Otago Human Ethics Committee (Health) (H19/004) and is registered with the Australian New Zealand Clinical Trials Registry (registration number: ACTRN12619000290190). Informed consent was obtained electronically from all participants via an online questionnaire [Research Electronic Data Capture (REDCap), production server version 9.3.3]. In addition, parental consent was obtained via email for participants who were under 16 years of age.

### Selection of Schools

Initially, secondary schools in the predetermined locations were selected to be invited to participate. Initial selection was made by selecting 2-5 schools per location, with a female roll number of at least 200. Lower decile schools (a measure of the socioeconomic status of the school) were preferentially selected for this round of invitation to ensure representation (Figure 1). The selected schools received emails and follow-up phone calls inviting them to participate. If the required number of schools was not reached through this method, other schools in the area were contacted and invited to participate. Schools that were interested provided written consent to participate (signed by an appropriate representative from the school).

### Recruitment of Participants

A brief information session (10-15 min) was delivered by the Master of Dietetics students to eligible pupils at each consenting school. At the session, pupils were given detailed information about the study and the required commitment. An expression of interest form was distributed for individuals to indicate their interest in participating by providing their email address. Individuals were also able to indicate interest on the study website [17]. Electronic and print information about the study was distributed at the school for anyone who required further information about the study. Individuals who provided their email address were sent a link to an online questionnaire (hosted on REDCap), on which they completed consent forms and answered a series of sociodemographic and general health questions. Participants who were under 16 years of age were asked to provide a parent’s email address and did not receive the link to the online questionnaire until a parent or guardian had consented to their participation.

### Inclusion Criteria

Adolescents who identify as female, are aged between 15 and 18 years, are enrolled in one of the selected secondary schools, can speak and understand English, and are not pregnant were eligible to participate.

### Sample Size

A sample size of 300 adolescent girls from 13 secondary schools will have 80% power to the *P*=.05 level to detect a 0.5 standard deviation difference (a “moderate” difference) in continuous outcome variables between vegetarians and nonvegetarians, assuming a prevalence of vegetarianism of 20% and a design effect (for school clusters) of 1.5. If the prevalence of vegetarianism is much less than 20%, then purposeful sampling of vegetarians was planned in the second half of the recruitment year.

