### Statistical Analysis

Statistical analyses will be carried out using Stata (StataCorp). School clusters will be accounted for in all analyses using appropriate methodology (for example, with a sandwich estimator or as a random effect). Estimates of prevalence and means will be reported with 95% confidence intervals. A binary variable for vegetarianism will be created, and comparisons between vegetarians and nonvegetarians will be carried out using regression models: linear regression for continuous outcomes and logistic regression for binary outcomes.

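### If vegetarians were topped up in the second half of the year, vegetarian status is tied to collection term, and the stated analysis adjusts for school only

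*Protocol article*

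**What the plan says.** The Sample Size section of the protocol article plans "A sample size of 300 adolescent girls from 13 secondary schools", powered "to detect a 0.5 standard deviation difference" between vegetarians and nonvegetarians, with 20% vegetarians and "a design effect (for school clusters) of 1.5". It adds a contingency: if the prevalence turns out to be much below 20%, "purposeful sampling of vegetarians was planned in the second half of the recruitment year". It gives no numerical trigger and no method for finding these girls.

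The Study Design section gives two collection windows: "Data were collected in the first (February to April) or third (August to October) term of school in 2019".

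The Statistical Analysis section states that "Estimates of prevalence and means will be reported with 95% confidence intervals". It compares the groups by linear or logistic regression on a binary vegetarian variable. School clustering is to be handled in all analyses, with a sandwich estimator or a random effect as examples. Term, recruitment route and weighting are not mentioned.

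The Results section reports that recruitment closed with 290 participants. It does not say whether the contingency was used.

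**The concern.** The contingency selects girls on the exposure, and in one half of the year only. If it was used, two things follow.

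- **Overall estimates.** The share of vegetarians in the pooled sample is partly set by recruitment. Any unweighted overall prevalence of vegetarianism moves with it. So does any whole-sample mean or prevalence of inadequate intake on which the groups differ.
- **Group comparisons.** A larger share of vegetarians than of nonvegetarians is seen in August to October. If an outcome differs between the terms, part of that difference enters the comparison. Diet and 24-hour activity, both listed objectives, could plausibly differ between late summer and late winter.

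Handling school as a cluster does not settle the second point. A sandwich estimator changes the standard errors and leaves the coefficient as it is. A random effect removes only part of a term difference.

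**Working it through.** **1. The plan's own figure.** Inputs from Sample Size: N = 300, 20% vegetarian, difference 0.5 SD, design effect 1.5, alpha 0.05 (two-sided assumed).
- Effective N = 300/1.5 = 200, that is 40 vegetarians and 160 nonvegetarians.
- SE = √(1/40 + 1/160) = 0.177 SD, and 0.5/0.177 = 2.83.
- Power = Φ(2.83 − 1.96) = 0.807.

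The stated 80% reproduces. The sample size is not in error.

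**2. What a top-up would do.** These inputs are assumptions and are not in the article: 150 girls per term; true prevalence p in the first term; second-term recruitment brings the total to 60 vegetarians of 300 (20%).
- Overstatement of vegetarian prevalence = 0.20 − p.
- Shift in a whole-sample mean, if the groups differ by 0.5 SD = (0.20 − p) × 0.5.
- Vegetarians seen in the later term = (60 − 150p)/60. Nonvegetarians seen in the later term = (150 − (60 − 150p))/240.
- Unadjusted bias in the comparison = difference between those two shares × assumed term shift.

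| p | Prevalence overstated by | Mean shift (SD) | Later term: veg / nonveg | Bias, 0.2 SD shift | Bias, 0.3 SD shift | Power with no top-up |
|---|---|---|---|---|---|---|
| 5% | 15 points | 0.075 | 88% / 41% | 0.09 | 0.14 | 34% |
| 9% | 11 points | 0.055 | 78% / 43% | 0.07 | 0.10 | 53% |
| 10% | 10 points | 0.050 | 75% / 44% | 0.06 | 0.09 | 56% |
| 12% | 8 points | 0.040 | 70% / 45% | 0.05 | 0.08 | 63% |
| 15% | 5 points | 0.025 | 63% / 47% | 0.03 | 0.05 | 71% |

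For p = 10%: 15 + 45 = 60 vegetarians; 45/60 = 0.75; 105/240 = 0.4375; difference 0.3125; 0.3125 × 0.3 = 0.094 SD.

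**3. Effect of the school adjustment at p = 10% and a 0.3 SD shift.** Assume each school is seen in one term, with 300/13 = 23.1 girls per school.
- Implied ICC = (1.5 − 1)/(23.1 − 1) = 0.023.
- A random-intercept model gives between-school information the weight λ = (1 − ICC)/1.5 = 0.65.
- Variance of vegetarian status within terms = (0.1 × 0.9 + 0.3 × 0.7)/2 = 0.15. Variance between terms = 0.1² = 0.01. Covariance with the term shift = 0.1 × 0.15 = 0.015.
- Bias = λ × 0.015/(0.15 + λ × 0.01).
- Sandwich estimator on an ordinary regression (λ = 1): 0.015/0.16 = 0.094 SD, unchanged.
- Random effect (λ = 0.65): 0.00975/0.1565 = 0.062 SD.
- If the term shift itself enters the estimated school variance, it adds 0.15² = 0.0225. The ICC becomes about 0.045, λ = 0.955/(1 + 22.1 × 0.045) = 0.48, and the bias is about 0.046 SD.

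So the random effect leaves about 0.06 SD or less, but not zero.

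**The case against.** Several stronger readings are tempting, and the article does not support them.

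- **That the top-up happened.** It is conditional, and neither Sample Size nor Results reports it as used. Distortion is a risk and not a fact.
- **That published overall figures will be wrong.** Statistical Analysis does not say whether prevalence and means are overall or by group. The objectives are group-wise, and vegetarian prevalence is not among them. Study Design already warns that a convenience sample may differ from the population. That caveat does not, however, disclose deliberate selection on the exposure.
- **That selecting vegetarians biases the comparison in itself.** It does not. Enriching a scarce exposure group is a standard way to protect power, and the last column of the table shows why it was planned. Bias needs a term effect on the outcome, or added girls who differ from other vegetarians. The article gives no evidence of either, and the idea that added girls hold stronger attitudes is conjecture.
- **That added girls came only from schools first visited in the later term.** The text fixes timing only. A return to first-term schools is not excluded.

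It can also be said that covariate lists belong in a full analysis plan, which is not shown, and that silence on term does not prove its omission. That is fair as far as it goes. What stands is that one section sets a selection rule tied to time, and another describes the analysis and adjusts for school alone. The article was written after recruitment closed, so whether the rule was used could have been stated.

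**Conclusion.** The point holds conditionally. If the top-up was used and the analysis follows the text, vegetarian status is associated with term, and unweighted overall estimates depend on recruitment. For assumed true prevalences of 15% down to 5%, overall vegetarian prevalence would be overstated by 5 to 15 points, and whole-sample means would move by 0.025 to 0.075 SD where the groups differ by 0.5 SD.

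The vegetarian v nonvegetarian comparison is affected only under the further condition of a term effect or a difference between added and other vegetarians. In the 10% illustration with a 0.3 SD term shift, the bias is about 0.09 SD unadjusted, or 19% of the 0.5 SD target (0.094/0.5), and about 0.06 SD or less with a school random effect. The prevalence, the equal halves, the top-up to 60 and the term shift are all assumed. This is modest, but it is avoidable with data already held.

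**What to change.** 1. Add term (first or third) as a fixed covariate in every vegetarian v nonvegetarian model, whichever method is used for school clustering.
2. State whether the top-up was used. If it was not, one sentence closes the question about overall estimates.
3. If it was used, flag the added girls. Base any overall vegetarian prevalence or whole-sample mean on routinely recruited girls, or weight the added girls back.
4. If it was used, repeat the comparisons without the added girls. Term adjustment cannot correct for added girls who differ from other vegetarians, so this run is the check on that.

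The cost is one flag, one school-level covariate and one extra run. In the 10% illustration, adjusting for term raises the variance of the comparison by 0.16/0.15 = 1.07, so the standard error rises by about 3%. The sensitivity run has less power. If the 105 later-term nonvegetarians came with routine vegetarians at 10%, there would be 105/0.9 = 116.7 routine girls in that term and about 27 vegetarians among 267 girls overall. After the design effect the SE is √(1/17.8 + 1/160) = 0.25 SD and power is about 52%. It should be read for the direction and size of the estimates rather than for significance.

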**Figure 1 figure1:**
[figure not shown]
Study Design.

### Outcome Measures

#### Online Questionnaire

Once participants completed enrollment, they were asked to complete an online questionnaire that follows from the enrolment questions on REDCap. This questionnaire is divided into three sections. The health and demographics section consists of 29 questions about sociodemographic characteristics and health status including current menstrual status, and food allergies or intolerances. It also asks participants if they identify as vegetarian. Initially, this was done by simply asking them, “Are you a vegetarian or vegan?” If they answered in the affirmative, they were asked to identify which of the following foods they eat: *Eggs, Milk, Fish or seafood, Chicken or poultry, Meat/red meat occasionally,* or *None of the above*. If they selected *None of the above*, they were asked if they identify as vegan. Participants were asked how long they have been following this way of eating, to which they could select options ranging from *less than a month* to *my whole life.* Adaptive questioning is used in this section so that, for example, if a participant answered “no” to “Are you a vegetarian?” they then moved on to the next question and did not see the questions pertaining to identifying as vegan or how long they have been following that eating pattern. The attitudes and motivations section includes 4 previously validated questionnaires [18-21] (Table 1) that, combined, consist of a total of 81 questions. In this section, questions that ask about similar concepts have been randomly distributed within each of the 4 questionnaires. Responses will be scored according to the published instructions [18-21]. The Dietary Habits section consists of 73 questions from the Dietary Habits Questionnaire that was used in the New Zealand Adult Nutrition Survey 2008/2009, which includes questions about weight loss intentions [22]. Each participant completed the questions from all sections in the same order, and an answer was required for each question. There was no timeframe limitation on completion. Participants were able to go back to previously answered questions and change their answers but there was no review step, and once the questionnaire was completed, they could not access it again. However, participants could leave the questionnaire at any point without completing it. A code was provided to participants so they could log back in and complete the questionnaire later, and reminders were sent to encourage them to do this. Incomplete questionnaires will be included in analysis on a case-by-case basis, depending on the outcome of interest.

**Table 1 table1:** Summary of outcome measures to be collected in the SuNDiAL Project.

Outcome				Assessment Method
